### Power analysis

Following best-practice procedures for LMM, power analysis was based on a Monte Carlo simulation. Based on pre-specified LMM model parameters, new values for the primary outcome were simulated and tested by z-tests for the comparison between study arms 1 and 3 (main hypothesis). This procedure was iterated 1000 times using simulated replicates. Power resulted from the number of significant effects identified across simulations (see [89]). The model parameters were derived from the CANreduce 2.0-RCT [19], due to its similar study design and measurements. We estimated a two-level Poisson generalized linear mixed model (GLMM) with random slopes and fixed effects for "measurement time", "study condition", and "condition*time". The CANreduce 2.0 model estimate yielded an effect of b = -0.069 (*p* = 0.07) for the interaction. This value was reduced to -0.06 for the power analyses to account for the smaller ES that have been established in meta-analyses [10]. The simulation indicated a power > 80% for *n* = 210 per study arm. Hence, a total sample of 630 frequent cannabis users will be targeted.

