#### Recruitment of study participants

Frequent cannabis users from the general population will be recruited directly through the website *canreduce.ch*, which is well-known since earlier versions of the program have been advertised broadly [19]. The target group also will be informed about the study via reports in community newspapers and posts on the national addiction internet-portal SafeZone.ch. Additionally, relevant healthcare professionals will be informed about the program via journals published by certain professional association to which they might belong (e.g., Swiss Medical Association FMH, Federation of Swiss Psychologists FSP) and related websites (e.g., praxissuchtmedizin.ch), as well as through direct mailings (including flyers to general practitioners, psychotherapists, and psychologists).

The recruitment phase, which has already started, began on September 13 2021 and will last until September 13 2023. The two-year duration of the recruitment phase should allow us to recruit the targeted sample size of 630 participants (see below). As detailed below, participants with sufficient knowledge of German are eligible to participate. Hence, even though the program is primarily advertised in the German-speaking part of Switzerland, it is possible that people from other parts of Switzerland, and from Germany and Austria will participate as well.

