## Discussion

To the best of our knowledge, this is the first RCT to test whether a self-help IMI that incorporates mindfulness is effective at reducing problematic cannabis consumption in adults (broad age range) with frequent cannabis use. Important limitations of previous research are taken into account; for instance, by aiming for a large enough sample size that allows us to detect even small ES. Furthermore, study arm 1 of CANreduce 3.0, which combines CBT and mindfulness, seeks to leverage the established effectiveness of IMI [10–13] (including previous versions of CANreduce [17, 20]) as well as mindfulness-based programs [33, 38–45] for the treatment of SUD (or frequent cannabis use, more specifically). It is possible that adding mindfulness to CANreduce 3.0 is particularly relevant for some subgroups of the population with certain clinical (e.g., co-occurring SUD and depression; [46, 47]) or sociodemographic characteristics (e.g. [48]). Furthermore, the RCT outlined here will provide significant insights into the questions of whether MBI can effectively be delivered via technology-based platforms and, by doing so, overcome some of the implementation challenges of traditional MBI [30]. More generally speaking, CANreduce 3.0 – if proven effective reducing cannabis use and related problems (e.g., symptoms of mental disorders) – could be of particular significance, as it could help to reach frequent cannabis users in the general population who are reluctant to seek traditional forms of help [8, 9] or lack access to similar programs (e.g., mindfulness programs offered in situ).

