Despite the potential advantages of CANreduce 3.0, the following limitations must be taken into account. First, and based upon previous research (e.g. [17]), relatively large drop-out rates are expected. Furthermore, it is possible that adherence to IMI is generally limited, due to the distant nature of such interventions [90]. However, according to the supportive-accountability model, [18] it is assumed that these issues have been somewhat ameliorated in CANreduce 3.0, via the addition of both a female and male eCoach. Secondly, it must be acknowledged that many contents in the modules offered in study arms 1 and 2 are provided in written form. Hence, a certain level of literacy is required. Thirdly, all measurements will be self-reported; and, though most of the measurements used have been validated in other clinical and research settings, they have not yet been validated as online assessments. On the other hand, participants in studies assessing previous versions of CANreduce also filled out questionnaires online, which did not seem to cause any (validity) issues.

In conclusion, we believe that version 3.0 of CANreduce will further our understanding of the effectiveness of IMI and MBI (and their combination) for the treatment of frequent cannabis users and will – if found effective – help to reach and support frequent cannabis users who might otherwise forgo care.

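### The power analysis states no allowance for drop-out, although the protocol expects substantial drop-out, so the power above 80% at 210 per arm is not supported at the retention the trial foresees

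*Protocol article*

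**What the plan says.** The Power analysis section describes 1000 simulated replicates of a two-level Poisson mixed model with random slopes. The condition-by-time effect is tested for arm 1 against arm 3, which the section names as the main hypothesis. The starting value comes from the preceding trial: "The CANreduce 2.0 model estimate yielded an effect of b = -0.069", with a p-value of 0.07. It is lowered to -0.06 "to account for the smaller ES that have been established in meta-analyses". The result is given only as a bound, "The simulation indicated a power > 80% for" 210 per arm, and the next sentence sets the total: "Hence, a total sample of 630 frequent cannabis users will be targeted".

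The Recruitment section confirms that this total counts people entering the trial, since the two-year window "should allow us to recruit the targeted sample size of 630 participants". Neither section gives a loss rate, an inflation factor or a missing-data pattern.

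The Discussion lists as its first limitation that "relatively large drop-out rates are expected". It also presents the design as "aiming for a large enough sample size that allows us to detect even small ES". Under Hypotheses, the main outcome is the change from baseline to 3 and 6 months. Under Data analyses, missing values are handled by multiple imputation with 20 data sets, under intention to treat.

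**The concern.** The number for which power was computed and the number to be recruited are the same, yet the authors predict that a material share of those recruited will not supply the outcomes on which the hypotheses rest. Multiple imputation keeps every randomised participant in the analysis, but it does not restore the information lost with a missing follow-up.

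This affects the comparison that decides the trial. If power at realistic retention is nearer 60% than 80%, a non-significant result for arm 1 against the waiting list says much less than a reader of the Power analysis section would suppose. The statement about small effects adds to this. It presents as settled something for which the article reports power at only one value of b.

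**Working it through.** **Reproducing the stated figure.** This is not possible from the article. The random-effect variances, baseline mean, time coding, significance level and missing-data pattern of the simulation are not given. An approximate calculation with assumed inputs (mean 15 to 25 days, several time codings) gives power from about 30% to above 90% as the random-slope SD runs from 0.4 to 0. A figure above 80% is therefore attainable, but it cannot be verified.

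**Inflation.** 3 x 210 = 630, so the allowance between the powered number and the recruited number is zero.

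**Effect of drop-out.** Inputs: 210 per arm (Power analysis); two-sided 5% level (assumed, because the article states it only for the comparison of arms 1 and 2); complete-data power of exactly 80% (assumed, the lower limit of the stated bound); proportion lost L (assumed, as the article gives no rate). Those lost are taken to contribute no follow-up information, so the information is multiplied by (1 - L).

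The standardised effect at full data is 1.960 + 0.842 = 2.802, and power = Φ(2.802 x √(1 - L) - 1.960):

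- L = 20%: Φ(2.506 - 1.960) = 71%
- L = 30%: Φ(2.344 - 1.960) = 65%
- L = 40%: Φ(2.170 - 1.960) = 58%
- L = 50%: Φ(1.981 - 1.960) = 51%

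**Room inside the bound.** If the simulated power was higher, some loss can be absorbed. The loss that brings power back to 80% is L = 1 - (2.802 / (1.960 + z))², where z is the normal quantile of the simulated power:

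- 85% simulated: 1 - (2.802 / 2.996)² = about 13%
- 90% simulated: 1 - (2.802 / 3.242)² = about 25%

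**Scale of the missing allowance.** Keeping 210 per arm with data would mean randomising 210 / 0.8 = 263 per arm at 20% loss, or 210 / 0.7 = 300 at 30%.

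**Sensitivity to b.** The cut from -0.069 to -0.06 is 0.009 / 0.069 = 13%. If power is 80% at -0.06 with complete data, power at another b is Φ(2.802 x |b| / 0.06 - 1.960):

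- b = -0.05: Φ(2.335 - 1.960) = 65%
- b = -0.04: Φ(1.868 - 1.960) = 46%

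The article reports no such range.

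**The case against.** The strongest reply is that nothing here shows the stated power to be wrong. It is only a lower bound, so a margin of unknown size may exist. The simulation took its parameters from a trial that had its own losses, and a condensed article may simply not mention that missingness was simulated. Some participants who are lost later will have 6-week or 3-month data, which a mixed model uses, so counting them as uninformative is pessimistic. Drop-out is disclosed, and retention is supported by payments at 3 and 6 months, telephone contact and triggered emails. The Design section also says that failure of both active arms could mean the trial is insensitive, which guards partly against over-reading a null result. All of this stands, and it makes the shortfall conditional. It does not supply the missing statement about what retention the power refers to.

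A reader might also infer that a 13% cut in b is plainly too small beside the standardised effects in the Background: 0.60 for the most effective CANreduce 2.0 arm, 0.20 for version 1.0 and 0.11 for earlier digital interventions. The documents do not support that inference. The coefficient b is a log-scale interaction with unreported time coding and cannot be converted to d. The 0.11 comes from source [12], whereas the cut cites source [10], whose effect is not quantified in the article.

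Nor can it be said that small effects are out of reach. An unadjusted two-group comparison at 210 per arm has 54% power for d = 0.20, but adjusting for baseline raises that to about 66% or 82% at an assumed correlation of 0.5 or 0.7. Working back from p = 0.07 settles nothing either, because it needs the size of the earlier trial, which is not given, and plausible sizes put power on both sides of 80%.

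**Conclusion.** The concern holds as a conditional one. The central planning figure carries no stated allowance for a loss that the same article predicts. If the simulation used complete data and gave about 80%, and those lost add no follow-up information, power for arm 1 versus arm 3 is about 71% to 51% over an assumed 20% to 50% loss. If the simulated power was 85% or 90%, the 80% level survives only up to about 13% or 25% loss. The loss rates are assumptions, since the article gives none.

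A reader might infer that the power above 80% is overstated as a matter of fact, or that there is an arithmetic error. Neither is shown: the multiplication is correct, and both the margin above 80% and the handling of missingness in the simulation are unknown. What can be said is that the figure is unsupported at the retention the authors expect, and that the statement about small effects lacks reported figures behind it.

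**What to change.** 1. Re-run the existing simulation at 210 randomised per arm, imposing the drop-out by visit seen in earlier CANreduce trials, and report that power in place of the present bound. If missingness was already simulated, say so and give the rate.
2. Report power over a range of b weaker than -0.06, for example -0.05 and -0.04, under the same drop-out.
3. Keep the Discussion's statement about detecting small effects only if those figures bear it out; otherwise remove it.

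The cost is one re-run of existing code and probably a less favourable stated figure. The recruitment target can stay at 630.

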## Discussion

To the best of our knowledge, this is the first RCT to test whether a self-help IMI that incorporates mindfulness is effective at reducing problematic cannabis consumption in adults (broad age range) with frequent cannabis use. Important limitations of previous research are taken into account; for instance, by aiming for a large enough sample size that allows us to detect even small ES. Furthermore, study arm 1 of CANreduce 3.0, which combines CBT and mindfulness, seeks to leverage the established effectiveness of IMI [10–13] (including previous versions of CANreduce [17, 20]) as well as mindfulness-based programs [33, 38–45] for the treatment of SUD (or frequent cannabis use, more specifically). It is possible that adding mindfulness to CANreduce 3.0 is particularly relevant for some subgroups of the population with certain clinical (e.g., co-occurring SUD and depression; [46, 47]) or sociodemographic characteristics (e.g. [48]). Furthermore, the RCT outlined here will provide significant insights into the questions of whether MBI can effectively be delivered via technology-based platforms and, by doing so, overcome some of the implementation challenges of traditional MBI [30]. More generally speaking, CANreduce 3.0 – if proven effective reducing cannabis use and related problems (e.g., symptoms of mental disorders) – could be of particular significance, as it could help to reach frequent cannabis users in the general population who are reluctant to seek traditional forms of help [8, 9] or lack access to similar programs (e.g., mindfulness programs offered in situ).

Despite the potential advantages of CANreduce 3.0, the following limitations must be taken into account. First, and based upon previous research (e.g. [17]), relatively large drop-out rates are expected. Furthermore, it is possible that adherence to IMI is generally limited, due to the distant nature of such interventions [90]. However, according to the supportive-accountability model, [18] it is assumed that these issues have been somewhat ameliorated in CANreduce 3.0, via the addition of both a female and male eCoach. Secondly, it must be acknowledged that many contents in the modules offered in study arms 1 and 2 are provided in written form. Hence, a certain level of literacy is required. Thirdly, all measurements will be self-reported; and, though most of the measurements used have been validated in other clinical and research settings, they have not yet been validated as online assessments. On the other hand, participants in studies assessing previous versions of CANreduce also filled out questionnaires online, which did not seem to cause any (validity) issues.

In conclusion, we believe that version 3.0 of CANreduce will further our understanding of the effectiveness of IMI and MBI (and their combination) for the treatment of frequent cannabis users and will – if found effective – help to reach and support frequent cannabis users who might otherwise forgo care.

## Data Availability

Not applicable.

## Abbreviations

CBT: Cognitive-behavioral therapy
CUD: Cannabis use disorder
CUDIT-R: Cannabis Use Disorders Identification Test-Revised
ES: Effect size
GLMM: Generalized linear mixed model
IMI: Internet- and mobile-based intervention
ITT: Intention-to-treat principle
LMM: Linear mixed models
MBI: Mindfulness-based intervention
MBRP: Mindfulness-based Relapse Prevention
MBSR: Mindfulness-Based Stress Reduction
MCMC: Markov chain Monte Carlo
MI: Motivational interviewing
MORE: Mindfulness-Oriented Recovery Enhancement
MTS: Mindfulness Training for Smokers
RCT: Randomized controlled trail
SDS: Severity of Dependence Scale
SUD: Substance use disorder
TAU: Treatment as usual
TLFB: Time-Line-Follow-Back
THC: Tetrahydrocannabinol
